### 2.6. Interventions and Comparators

Each patient will attend their scheduled healthcare appointment with their physician and receive their healthcare as planned and permitted. During each appointment, in random sequence, the physician will deliver P3-EX to one patient and PAVS to the other patient.

#### 2.6.1. Delivery of the *P*rioritizes *P*ersonalizes *P*rescribes *EX*ercise (P3-EX) ExRx

Physicians will use P3-EX (version 1.0.0, P3-EX LLC, Wethersfield, CT, USA) hosted on a web-based platform to deliver a personalized ExRx for improving cardiovascular health [32]. Figure 2 provides a workflow of the P3-EX algorithm.

In Step 1, the physician will enter the patient’s PA levels, presence of signs/symptoms of or having cardiovascular, metabolic, or renal disease, and desired exercise intensity. P3-EX will determine the need for medical clearance [33]. The physician will then enter the patient’s CVD risk factor values related to obesity, hypertension, dyslipidemia, and diabetes. In Step 2, P3-EX will score the patient’s CVD risk factors using an adapted AHA Life’s Essential 8 cardiovascular health scoring system to determine the CVD risk factor posing the greatest risk [22]. If ≥2 CVD risk factors are tied for the greatest risk, P3-EX will prompt the physician to choose an ACSM strategy, using their clinical judgment, to prioritize 1 CVD risk factor to personalize the FITT ExRx that is either (A) the most limiting, (B) the most conservative, or (C) encompasses the FITT of other CVD risk factors [22]. In Step 3, P3-EX will produce a personalized FITT ExRx and special exercise considerations for the prioritized CVD risk factor [25]. The physician will print and give the ExRx to the patient.

#### 2.6.2. Delivery of the Physical Activity Vital Sign (PAVS) ExRx

Physicians will use a hard copy instruction manual adapted from the Exercise is Medicine HealthCare Providers’ Action Guide [47] to deliver a generic ExRx for improving general health [48]. In Step 1, the physician will ask exercise preparticipation health screening questions to the patient to determine the need for medical clearance [33]. In Step 2, the physician will assess their patient’s PA levels as a vital sign (i.e., minutes per week of moderate to vigorous intensity exercise and days per week of resistance exercise) [8]. In Step 3, the physician will give the patient a PAVS handout [48], which recommends the PA guidelines for Americans of 150 min per week of moderate and/or 75 min per week of vigorous intensity aerobic exercise or a combination of both and 2 days per week of muscular strengthening exercise [44].

#### 2.6.3. 12-Week Exercise Intervention

[name], an ACSM-certified exercise professional, with assistance from RAs, will provide patients with virtual weekly oversight of their unsupervised ExRx for 12 weeks, performed at a location the patients prefer. During the first week, [name] will email all patients to provide a 12-week ExRx information packet (Supplementary File S3) containing standardized and progressive FITT exercise recommendations for the ExRx they received [25], and patients will attend a one-on-one virtual study visit led by [name] over Microsoft Teams to receive standardized exercise guidance. [name] will use a script to walk patients through exercise definitions and examples and how to monitor exercise intensity and progress the FITT of exercise. Throughout the intervention, [name] will email all patients weekly to provide their ExRx FITT exercise goals for the upcoming week. Patients will use a validated exercise diary called the *Timeline Followback for Exercise* (TLFB-E) [49] to record the FITT of exercise they perform daily for the 12-week exercise intervention. [name], with assistance from RAs, will monitor the TLFB-E for each patient to assess their adherence to the intervention and challenges they may be having. [name] will email all patients with weekly feedback by providing their TLFB-E summary report from the previous week. After completing 6 weeks of the intervention, patients will attend a second one-on-one virtual study visit led by [name], using a script, to inform patients how they are faring following their ExRx by reviewing their TLFB-Es and strategies to improve exercise adherence.

### 2.7. Primary Outcome Assessment

#### Feasibility and Acceptability of P3-EX

The mHealth Application Usability Questionnaire, developed by Zhou et al. (2019) [50], is validated to measure the usability of mobile health apps for healthcare providers and/or patients on 21 items separated into three subscales: Ease of Use and Satisfaction, System Information Arrangement, and Usefulness. The three subscales and the overall scale demonstrate high internal consistency and strong correlation with other validated usability questionnaires [51,52]. Physicians and patients will complete the interactive versions of the questionnaire [50], including open-ended written questions, within 48 h following the use of P3-EX and PAVS, administered by [name] via email. To appropriately rate P3-EX and PAVS, we adapted question 13 to remove language that is not applicable (e.g., “responding to reminders”), and for patients to rate their ExRx, we adapted questions 3 and 13 to replace the word “interface” with “look” and “format”, respectively. The rating of each item is scaled from 1 to 7 (strongly disagree to strongly agree), and responses are averaged to provide a single score, with 7 reflecting the highest usability and 0 reflecting the lowest [50]. P3-EX will be interpreted as feasible and acceptable for physicians to use if overall scores exceed the middle score of 4.0 on the questionnaire scale [50].

The System Usability Scale [51] is the most commonly used and validated questionnaire to assess the usability of mHealth apps [53], demonstrating acceptable reliability across numerous usability studies [52]. Physicians and patients will complete the original English version of the questionnaire developed by Brooke (1986) [51] within 48 h following the use of P3-EX and PAVS, administered by [name] via email. Ratings for each of the 10-items range from 1 to 5 (strongly disagree to strongly agree), and the unique score contribution for each item is summed to yield a single score ranging from 0 to 100, with 100 reflecting the highest usability and 0 reflecting the lowest [51]. P3-EX will be interpreted as having above average usability if the overall score exceeds the normative reference score of 68 [54].

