### 2.13. Sample Size Estimation

We conducted a power analysis using G*Power (version 3.1.9.6, Heinrich Heine University Düsseldorf, Düsseldorf, Germany) [68] to obtain a conservative usability rating of P3-EX to evaluate the primary aim of the study. We obtained the lowest observable usability score of 4.650 ± 0.759 (mean ± SD) converted from our feasibility survey study pilot data [32] to compare to the null hypothesis middle score of 4.0 on the mHealth Application Usability Questionnaire [50]. Using a one-sided Wilcoxon signed-rank (one sample case) test [69] at the significance level (α) of 0.01 and calculated effect size between the observed and middle score of Cohen’s d = 0.856, we determined that 19 physicians are required to achieve 85% power. Therefore, we will use 19 physicians to achieve 85% power (α of 0.01), and recruit two patients per physician to complete 38 patients. Using an observed attrition of 20% for patients in the study [70,71,72,73], this trial will aim to recruit 24 physicians and 48 patients (24 patients per group). Because physicians’ PA levels could influence how they perceive and rate the delivery of an ExRx [45], we aim to recruit half of the physicians who meet PA guidelines (n = 12) [44] and half who do not (n = 12).

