### 2.14. Statistical Analysis

The statistical analysis plan for this trial is accessible on ClinicalTrials.gov. Statistical analyses will be conducted by [name] using Statistical Package for the Social Sciences (version 30, IBM Corp., Armonk, NY, USA) [74] with oversight from [name], [name], [name], [name], and [name], with [name], [name], [name], and [name] being blinded to group assignments. We will first use descriptive statistics and graphical techniques to ensure all test assumptions are met, including the inspection for outliers, normal distributions [75], and homogeneity of variances [76]. Missing values will be addressed using model-based approaches and/or multiple imputations when appropriate to include the entire randomized sample [77]. If normality assumptions are not met for secondary outcomes, considerations will be made to transform the data to achieve a normal distribution or use alternative non-parametric approaches such as permutated tests. An alpha level of 0.05 will be used to determine statistical significance.

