#### 2.14.1. Evaluation of the Primary Aim

We will use the following statistical approaches to evaluate the feasibility and acceptability of P3-EX for physicians to use to prescribe exercise to patients with CVD risk factors. We will use a one-sided Wilcoxon signed-rank (one sample case) test [69] to assess whether the physician mHealth Application Usability Questionnaire ratings of P3-EX and the PAVS are above the null hypothesis middle score of 4.0 on the Likert scale [50], and whether System Usability Scale ratings are above the average score of 68/100 [78]. We will use a linear mixed effects model adjusting for the delivery order of P3-EX and PAVS and the time between delivery as potential covariates and interactions between these two covariates to assess differences in the physician usability questionnaire scores between P3-EX and the PAVS. We will use normal linear regression to determine the strength of relationships between the three domains on the mHealth Application Usability Questionnaire and usage time of P3-EX and PAVS.

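### Section 2.7 lets a bare score above 4.0 decide that P3-EX is feasible and acceptable, without linking this to the Wilcoxon test of 4.0 in 2.14.1, whose alpha is itself given as both 0.01 and 0.05

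*Protocol article*

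**What the plan says.** Section 2.7 of the protocol article covers two usability questionnaires as primary outcomes. For the mHealth Application Usability Questionnaire it says "P3-EX will be interpreted as feasible and acceptable for physicians to use if overall scores exceed the middle score of 4.0" on that scale. For the System Usability Scale it says "P3-EX will be interpreted as having above average usability if the overall score exceeds the normative reference score of 68". Neither sentence mentions a test, a confidence bound or an alpha, and neither says whether the score across physicians is a mean or a median.

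Section 2.14.1 sets out the analysis of the primary aim: "We will use a one-sided Wilcoxon signed-rank (one sample case) test". It asks whether the physician mHealth ratings "are above the null hypothesis middle score of 4.0 on the Likert scale" and "whether System Usability Scale ratings are above the average score of 68/100".

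Section 2.13 sizes the trial on this test for the mHealth questionnaire alone, "at the significance level (α) of 0.01", and arrives at 19 physicians for 85% power. Section 2.14 then states: "An alpha level of 0.05 will be used to determine statistical significance". It makes no exception for the primary test.

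**The concern.** One conclusion has two criteria. Section 2.7 compares an observed score with 4.0. Section 2.14.1 asks whether the ratings lie above 4.0 by more than chance would explain. The article does not say that the first requires the second, so an investigator with a mean of, say, 4.1 could follow 2.7 and declare success, or follow 2.14.1 and report a non-significant result. Both would be within the published plan.

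A reader who settles on the test then has to choose between alpha 0.01 and alpha 0.05, which moves the bar again. This is the trial's headline claim, and the choice between the readings would be made after the data are seen unless the text fixes it now.

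**Working it through.** **Inputs (all from 2.13 unless noted).** Null value 4.0; assumed mean 4.650; SD 0.759; one-sided alpha 0.01; 19 evaluable physicians; 85% power; 24 recruited. Alternative alpha 0.05 from 2.14.

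**1. The article's own figure.** Effect size: (4.650 − 4.0)/0.759 = 0.856, as stated. Power was taken from the one-sample noncentral t with n multiplied by the Wilcoxon relative efficiency for a normal parent (3/π). At one-sided alpha 0.01 and n = 19 this gives 84.8%. A simulation of 100,000 trials with exact Wilcoxon critical values gives 84.6%. The stated 19 physicians for 85% is reproduced within rounding. With 20% attrition, 19/0.8 = 23.75, hence 24.

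**2. Observed mean needed under each reading.** The signed-rank test has no fixed critical mean, so the t approximation is used: 4 + t × SD/√n.

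- n = 19: SE = 0.759/√19 = 0.174.
  - Section 2.7 as worded: above 4.00.
  - Alpha 0.05: 4 + 1.734 × 0.174 = 4.30.
  - Alpha 0.01: 4 + 2.552 × 0.174 = 4.44.
- n = 24: SE = 0.759/√24 = 0.155.
  - Alpha 0.05: 4.27.
  - Alpha 0.01: 4.39.

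For example, an observed mean of 4.1 at n = 19 gives t = 0.1/0.174 = 0.57, one-sided p about 0.29. It meets 2.7 and is far from significant at either level. At alpha 0.01 the band in dispute is 0.44 wide, and 0.44/0.65 = 0.68 of the effect for which the trial was powered.

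**3. Chance of passing under each reading.** For the bare cut-off applied to a mean, P(pass) = 1 − Φ((4 − μ)/(SD/√n)).

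| True mean | 2.7 alone, n = 19 | 2.7 alone, n = 24 |
|---|---|---|
| 4.0 | 50% | 50% |
| 3.9 | 28% | 26% |
| 3.8 | 13% | 10% |

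Reading the score as a median leaves the first row at about 50% (simulated 50.3% and 50.0%). A larger sample does not lower it.

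Under the planned Wilcoxon test, a tool centred on 4.0 passes with these simulated probabilities:

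- Alpha 0.01: 0.9% (n = 19), 1.0% (n = 24).
- Alpha 0.05: 4.8% at either n.

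**4. Power if the test decides.** At the assumed mean of 4.65 and alpha 0.01, the test rejects about 85% of the time with 19 physicians and about 94% with 24. At alpha 0.05 and n = 19 it rejects about 97% of the time, and 12 physicians would already give 85%. The figure of 19 therefore belongs to 0.01, not to 0.05.

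**The case against.** The strongest reply is that 2.7 is an outcome section. It describes each instrument and its reference value, and the method of decision is in 2.14.1, which introduces its tests as the means of evaluating feasibility and acceptability. Section 2.13 calls 4.0 the null value and sizes the trial on the test. Putting the reference value in one section and the test of it in another is ordinary article structure. Much of this stands: it is the sensible reading, and very probably the intended one. It does not close the gap, because the sentence in 2.7 is the only one that says when P3-EX will be called feasible and acceptable, it contains no inferential condition, and no other section supplies one. Nor does it settle which alpha applies.

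Two stronger readings are tempting and are not supported:

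- A reader might infer that the trial lets a neutral tool pass half the time. That holds only if 2.7 is applied literally and the test in 2.14.1 is ignored. Any cut-off without a test passes a tool centred on it about half the time. With the planned test the rate is about 1% or 5%.
- A reader might infer that two primary questionnaires compete for the same conclusion with no ranking. The two cut-offs carry different labels. Only the mHealth questionnaire defines feasible and acceptable, and only it was powered. A score on one side of 4.0 and the other side of 68 would yield two different statements, not a contradiction. A formal hierarchy may also be in the statistical analysis plan, which is not shown here.

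**Conclusion.** The concern holds as an unlinked decision rule with an unreconciled alpha. For 19 physicians with SD 0.759, observed means from 4.00 up to about 4.30 (alpha 0.05) or 4.44 (alpha 0.01) count as success under 2.7 and are not significant under 2.14.1. Means between about 4.30 and 4.44 are also significant or not according to whether 2.14 or 2.13 supplies the alpha.

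These limits use the t approximation to the signed-rank test, roughly normal scores, and the pilot SD, and they widen or narrow in proportion to the SD actually seen. If scores come out near the assumed 4.65, all readings will usually agree. The ambiguity matters when the result is marginal, and that is when the rule most needs to be fixed in advance. The sample size calculation itself is sound.

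**What to change.** In 2.7, state that P3-EX will be called feasible and acceptable for physicians only if the one-sided Wilcoxon signed-rank test in 2.14.1, applied to the physician mHealth questionnaire ratings, rejects 4.0 at the one-sided 0.01 level used in 2.13. In 2.14, exempt this test from the general alpha of 0.05. Reword the System Usability Scale sentence in the same test-based form for 68, and label it a supportive result.

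The cost is wording, plus a stricter bar: a score only just above 4.0 would no longer be reported as success. No extra physicians are needed, since this is the test and level for which the trial was sized.

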### 2.8. Secondary Outcomes Assessments

#### 2.8.1. Physician ExRx Barriers to and Confidence with ExRx

Physicians will complete an adapted ExRx self-reflection questionnaire developed by O’Brien & Fowles (2017) [55] before completing the brief ExRx training and within 48 h following the delivery of either P3-EX or PAVS, to assess the impact of the trial on their perceived barriers to and confidence with ExRx. O’Brien & Fowles (2017) developed the questionnaire from a national survey and educations programs, given there are no previously validated questionnaires assessing ExRx barriers and confidence [55]. We adapted one question to be applicable for the study (i.e., ability to conduct PA screening instead of PA referral). Responses will be rated on a Likert scale from 1 to 4, with 4 indicating the highest impact from a barrier or the highest confidence with a skill and 1 indicating the lowest impact or confidence, and responses will be averaged to provide overall scores for ExRx barriers and confidence.

#### 2.8.2. AHA Life’s Essential 8 Cardiovascular Health Score

Patients will complete the validated AHA Life’s Essential 8 questionnaire [56] developed by Lloyd-Jones et al. (2022) to predict cardiovascular health [34], administered by [name], to assess the metrics of diet, PA, nicotine exposure, and sleep health via survey questions, and assessments of body mass index, blood pressure, blood lipid-lipoproteins, and blood glucose at pre- and 12 weeks post-intervention. Cardiovascular health scores ranging from 0 to 100 points will be calculated using the AHA Life’s Essential 8 criteria for each metric, to calculate an unweighted average of metrics and provide a single score [34]. Higher scores are associated with reduced risk of all-cause and CVD mortality [57].

#### 2.8.3. Resting Blood Pressure and Heart Rate

Patients will be asked to abstain from exercise for 2 days prior to, alcohol for 1 day prior to, and caffeine on the day of the blood pressure measurement. Resting systolic and diastolic blood pressure (mm Hg) and resting heart rate (bpm) will be assessed by [name] at pre- and 12 weeks post-intervention via automatic monitors (OMRON HEM-705CP, Omron Corporation, Kyoto, Japan and Polar F7, Polar Electro Oy, Kempele, Finland, respectively) [40]. After patients have sat for 10 min, [name] will take three heart rate and blood pressure measurements 1 min apart and average them [58]. [name] will take blood pressure measurements in the patients’ nondominant arm until 3 measurements agree within 5 mmHg [59].

#### 2.8.4. Body Mass Index and Waist Circumference

Patient waist circumference (cm), height (m), and weight (kg), and body mass index (kg/m^2^) will be assessed by [name] at pre- and 12 weeks post-intervention via a Gullick tape measure (M-22CII, Country Technology, Inc., Brookfield, WI, USA) and a mechanical beam balance scale with stadiometer (Health o meter, Pelion, IL, USA), respectively [39]. Body composition assessments will be measured in duplicate and averaged.

#### 2.8.5. Blood Lipid-Lipoproteins and Glucose

Fasting laboratory assessments will be conducted by phlebotomy technicians and processed at convenient Quest Patient Service Centers. Patient total cholesterol, triglycerides, high-density lipoproteins, low-density lipoproteins (mg/dL), glycated hemoglobin (%), and fasting plasma glucose (mg/dL) will be assessed at pre- and 12 weeks post-intervention [41,42].

#### 2.8.6. Subjective PA Levels and Exercise Adherence

Patient self-reported PA levels will be assessed at pre-intervention, and weekly for the 12-week exercise intervention via the TLFB-E. The TLFB-E is a validated calendar diary method [49] for recording the FITT of exercise, whereby, frequency is the number of days per week that PA is performed; type is the modality of PA performed (e.g., walking, lifting weights); time is the duration of each session performed in minutes for each modality; and intensity will be assessed using the Borg 6–20 rating of perceived exertion scale [60]. [name] and RAs will cross reference self-reported frequency, intensity, and time values on the TLFB-E with the 2024 Adult Compendium of Physical Activities [61] and accelerometer data to determine the agreement and verify atypical or unrealistic values. For each recorded PA, [name] and RAs will assign a metabolic equivalent value from the PA compendium to calculate the PA volume performed (MET·min/wk).

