#### 2.5.3. Blinding

[name], who will conduct physician and patient enrollment and pre- and post-intervention outcome assessments, will not have access to the random allocation sequence. [name] will be blinded to group assignments during patient pre-intervention outcome assessments, and laboratory technicians will be blinded when assessing all blood lipid-lipoprotein and glucose values. Patients will disclose details of their healthcare appointment to [name] after completing all pre-intervention outcome assessments.

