### 4.3. Limitations

We acknowledge potential limitations with the P3-EX Feasibility Trial. Physicians may experience burden of recruiting two of their patients to participate in the study. However, given that preventive care is one of the most common reasons for office-based physician visits [81], we anticipate that a high proportion of patients will be eligible. Concerning blinding, other than laboratory technicians assessing blood lipid-lipoproteins and glucose, we will not include other blinded outcome assessors. [name] will have knowledge of patient group assignments when conducting patient exercise guidance virtual visits and assessing vitals, body composition, and objective and subjective PA levels at post-intervention. [name] will therefore follow standardized laboratory operating procedures [59,65,66] to minimize observer bias, which include following outcome measurement protocols, providing privacy to patients during in-person survey completions, and reading standardized exercise guidance scripts. Although the TLFB-E is potentially susceptible to social desirability bias, we will cross reference the TLFB-E with the accelerometer at pre- and post-intervention. Last, concerning the study design, the trial does not include a non-exercise control group, which may hinder the ability to interpret the efficacy of P3-EX for improving patient PA levels or CVD risk factors. Nonetheless, this pilot data will inform the efficacy of P3-EX compared to generic ExRx approaches in routine medical care.

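### Diary entries are converted to MET values, and atypical entries checked, with no masking to arm, although this desk step could be scripted and masked at little cost

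*Protocol article*

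**What the plan says.** **The coding step (2.8.6).** Patients record the modality, the minutes and a Borg 6–20 exertion rating. Staff then turn each entry into activity volume: "For each recorded PA, [name] and RAs will assign a metabolic equivalent value from the PA compendium". The lead assessor and RAs also compare the diary with the Compendium and the accelerometer, "to determine the agreement and verify atypical or unrealistic values".

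**Who knows the arm.** Section 2.5.3 states that the lead assessor "will be blinded to group assignments during patient pre-intervention outcome assessments". It does not extend this to follow-up. Section 4.3 says that this person "will have knowledge of patient group assignments when conducting patient exercise guidance virtual visits and assessing vitals, body composition, and objective and subjective PA levels" after the intervention. The same section adds that "other than laboratory technicians assessing blood lipid-lipoproteins and glucose, we will not include other blinded outcome assessors".

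**Contact during the 12 weeks (2.6.3).** The lead assessor, "with assistance from RAs, will monitor the TLFB-E for each patient to assess their adherence", oversees the patients each week. The lead assessor also "will email all patients weekly to provide their ExRx FITT exercise goals for the upcoming week", and those goals depend on the prescription that the patient received.

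**Safeguards stated.** Section 2.11 refers to standardized operating procedures for the activity outcomes and says that the lead assessor trains the RAs. Section 4.3 lists measurement protocols, privacy for surveys, scripted guidance, and a comparison of diary with accelerometer before and after the intervention.

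**The concern.** Choosing a Compendium value for a diary entry involves some judgement. A modality and an exertion rating narrow the choice but need not fix it. Deciding which entries look atypical, and what to do with them, is a second judgement. At least one of the people making both judgements knows the arm.

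If the choices differ slightly but consistently by arm, P3-EX and PAVS will differ in MET·min/wk with no difference in what patients did. Subjective activity is named in the secondary aim (1.2), change in activity is compared between arms (2.14.2), and the Conclusions say that the secondary data will be used to power a larger trial. A coding artefact could therefore carry into that trial's assumed effect. The Abstract says that the team developed P3-EX, so arm-blind coding would also help credibility.

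Blood pressure after the intervention is taken face to face, by someone who has also delivered guidance to the patient. Assigning a MET value need not involve the patient at all.

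**Working it through.** The article gives no figure for this point: no coding agreement, no range of MET values per activity, and no SD for MET·min/wk. The check is therefore mainly a reading of the sections against each other. The arithmetic that follows is illustrative and rests on assumed inputs.

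**1. Is the coding masked?**
- *Lead assessor:* masked for pre-intervention assessments only (2.5.3). Section 4.3 says that this person knows the arm in the guidance visits, the first of which is in week 1 (2.6.3), and when assessing subjective activity after the intervention. Coding of the 12 diary weeks is thus not masked for this person.
- *RAs:* no section states that they are blinded, and 4.3 says that there are no blinded assessors outside the laboratory. No section states that they know the arm either. Their access to de-identified REDCap data (2.12) does not settle it, because de-identified data can still show arm or prescription.
- *Analysis oversight:* some of those overseeing the analysis are blinded (2.14), but that acts after the values have been coded.

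**2. Do the stated safeguards reach this step?**
- Survey privacy and guidance scripts concern contact with the patient.
- The measurement protocols and operating procedures may cover coding, but are not said to mask it.
- The accelerometer is worn before and after the intervention (2.8.7), so most of the 12 diary weeks have no device record to compare. The comparison is also made by the same staff (2.8.6).

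**3. Can the step be masked?** Diaries are entered electronically in REDCap (2.11), so an export without arm or prescription looks practicable.

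**4. Illustration of size (all inputs assumed).** Volume = minutes per week × MET value.
- 150 × 3.5 = 525 and 150 × 4.3 = 645 MET·min/wk; 645/525 − 1 = 0.229, or 23%.
- 150 × 3.0 = 450 against 525 MET·min/wk; 525/450 − 1 = 0.167, or 17%.
- If one coding in four drifts this way in one arm only, that arm's mean moves by 0.167/4 = 4.2% to 0.229/4 = 5.7%.

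**5. Illustration of false-positive risk (assumed shifts in SD units).** Take a two-group t-test at two-sided 5%, no true effect, and a coding shift of b SD between arms. The statistic is noncentral t with 2n − 2 degrees of freedom and noncentrality b√(n/2). For b = 0.2 and n = 24, the noncentrality is 0.2 × √12 = 0.69.

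| Assumed shift b | 24 per group | 19 per group |
|---|---|---|
| 0.1 SD | 6.3% | 6.0% |
| 0.2 SD | 10.4% | 9.2% |
| 0.3 SD | 17.4% | 14.7% |

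The planned model is a mixed model, so these rates are indicative only. Steps 4 and 5 cannot be joined: without an SD for MET·min/wk, a 4% to 6% shift cannot be expressed in SD units.

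**The case against.** The strongest reply is that the authors have already said this. Section 4.3 admits that no one outside the laboratory is a blinded assessor, names subjective activity among the outcomes concerned, and lists mitigations. No section contradicts another. That stands as a defence of the reporting. It does not answer why a step that can be masked is left unmasked.

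Second, a coding table and a query log are operational detail, which an article may leave to the full protocol or to the operating procedures in 2.11. That is fair, and their absence from the article is not the point. The point is a choice that the article does state: who codes, and that assessors are not blinded.

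Third, values come from a published compendium, so discretion is limited; accelerometry gives a separate measure that needs no MET coding; and the outcome is one of many in an exploratory aim. All of this stands and limits the weight of the point.

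Fourth, masking would be imperfect. The same staff look at the diaries every week, and the recorded exercise may hint at the arm. This also stands. It is the reason for making a scripted table the main safeguard, since the table gives the same answer whoever runs it.

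A reader might go further and infer that the RAs are known to be unblinded, or that the authors call unblinding unavoidable. The article supports neither. It is silent on what the RAs know, and 4.3 says only that other blinded assessors will not be included.

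**Conclusion.** The point holds as an avoidable weakness in how one secondary outcome is derived. The lead assessor's knowledge of the arm is explicit; that of the RAs is an inference from their role and from the absence of any stated blinding. The disclosed mitigations are not said to mask MET coding or the checking of atypical entries.

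The size of any bias is unknown, and so is its direction. The 17% to 23% per coding, the 4% to 6% in an arm's mean and the false-positive rates above all depend on assumed inputs. A reader might take them as evidence that the MET·min/wk comparison will be biased, or biased toward P3-EX. The documents do not show that.

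The primary physician usability analysis and the sample size are unaffected. The change is worth making before the first diary is coded because it is cheap and because the secondary data are meant to inform a larger trial.

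**What to change.** Add to 2.8.6, in words such as:

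> MET values are taken from a fixed table of modality by Borg band, written before the first diary is coded and applied by script to all patients. Activities not in the table, and atypical entries, are resolved on an export that carries a neutral random code and omits arm and prescription. The accelerometer data carry the same code, so that the two can be compared. Where possible this is done by an RA who does not take part in that patient's weekly oversight. Original values are kept and every change is logged.

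The linking code matters: an export with no identifier at all would prevent the accelerometer comparison that 2.8.6 plans. Weekly diary feedback to patients can continue as described. Any correction that arises from it should go into the same log.

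**Cost.** A few hours to write the table and set up the export and code. No extra staff, and no change to visits, sample size or clinical care.

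**Downsides.** The coder cannot use knowledge of the patient to interpret a free-text activity. The exercise pattern may still suggest the arm. Patients' own reporting bias, which 4.3 acknowledges, remains.
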